### Safety

Throughout the study, safety information will be collected for the intention-to-treat population by recording serious adverse events (AE) regardless of their causal relationships to the trial drugs and protocol. Upon confirmation of these AEs, the investigators will assess their severity or grade, the procedures conducted, the outcomes, and the relationships to the study drug. Investigators will immediately report AEs to the secretariat who, in turn, will promptly report to them to the principal investigator. In accordance with the Clinical Trial Act in Japan, the principal investigator must report all AEs suspected of having causal relationships with the study to the CRB at Saga University. The CRB will then independently evaluate trial safety, determine the requirement for revisions to the trial design, and validate all decisions to continue the trial. The criteria governing trial withdrawal are listed in Table 2.

**Table 2 Tab2:** Discontinuation criteria

Participant withdrawal of consent
Serious violation of study protocol
Considered inappropriate to continue the trial by investigators due to following conditions:
Severe hypoglycemia
Development of diabetic ketoacidosis
Serious dehydration requiring rehydration therapy
Seriously poor glycemic control (HbA1c ≥ 10.0%)
Aggravation of primary disease or complications
Adverse side effects of the trial drug
Other reasons
Discontinuation of ipragliflozin or use of other SGLT2is in the ipragliflozin group
Use of SGLT2is in the control group
Serious violation of study protocol
Participant withdrawal of consent

*SGLT2is* sodium glucose cotransporter 2 inhibitors

### Statistical considerations

#### Sample size estimation

The effects of SGLT2is on peripheral endothelial function remain to be elucidated as the currently available evidence is very limited. Sugiyama et al. [38] used RH-PAT to assess the effects of the SGLT2 inhibitor dapagliflozin on endothelial function in Japanese patients with uncontrolled T2D (baseline HbA1c, 7.9%; baseline eGFR, ~ 74 mL/min/1.73 m^2^; unknown cardiovascular event history). The sample size was estimated to detect mean differences of 0.15 and 0.05 in the change in LnRHI for the dapagliflozin and non-SGLT2 inhibitor group, respectively. The estimated group difference was 0.10, the standard deviation was 0.15, the power was 90%, and the two-sided α was 0.05. As a result, 6 mo of dapagliflozin treatment significantly improved endothelial function. The actual difference between the dapagliflozin and non-SGLT2 inhibitor groups in terms of LnRHI was 0.139. On the other hand, the aim of the present trial is to evaluate the effects of ipragliflozin on the aforementioned endpoint in patients with CKD. Compared to those in the study population of Sugiyama et al., these individuals may present with more advanced cardiovascular damage that is difficult to ameliorate using the available interventions. Thus, we estimated a difference of 0.10 ± 0.15 between the groups in terms of the change in LnRHI. At α = 5% for a two-sided test, a sample size of 98 patients was needed to provide a power of 90% for each comparison. Considering a potential dropout rate of 12%, it was estimated that ≥ 110 patients (55 patients per arm) would provide sufficient statistical power for the trial.

#### Statistical analysis plan

Summary statistics will be used to calculate all baseline characteristics including the categorical variable frequencies and proportions and the normally distributed mean ± standard deviation or median [interquartile range] with skewed distribution for the continuous variables. Patient characteristics will be compared by Fisher’s exact test for categorical variables and the Wilcoxon rank sum test for continuous variables.

Analyses of the primary and secondary endpoints will be performed for the full analysis set (FAS). The FAS excludes all participants with no post-randomization efficacy endpoint data and those deemed ineligible after registration because they failed to provide informed consent or did not meeting the study eligibility criteria.

The primary endpoint was a comparison of treatment effects between treatment groups. The baseline-adjusted least-square means (LSM) and their 95% confidence intervals (CI) will be estimated by analysis of covariance (ANCOVA) for the FAS. For a secondary analysis of the primary endpoint, an analysis of variance including allocation factors and treatment group as factors will also be performed. As a supplementary analysis, the primary endpoint will also be analyzed in the per protocol set excluding subjects seriously violating the trial protocol. Prespecified subgroups stratified according to clinical characteristics based on, but not limited to, the RHI at baseline (< 1.67 or ≥ 1.67) will be analyzed for the primary endpoint as described above.

For the secondary endpoints, (i) the % change in LnRHI from baseline to 24 wks or discontinuation will be analyzed by a two-sample *t* test. Their LSMs and 95% CIs will be calculated and the treatment effects will be compared between groups. (ii) The proportions of patients presenting with clinically meaningful changes in LnRHI or RHI will be analyzed with a logistic regression model adjusted by the corresponding baseline values to calculate the odds ratios and their 95% CIs and compare the treatment effects between groups.

Changes in the additional efficacy endpoints from baseline to 24 weeks or discontinuation will be analyzed by ANCOVA as for the primary endpoint. The LSMs and their 95% CIs will be calculated and the treatment effects will be compared between groups. Pearson’s correlation coefficients will be used to identify the correlations between the changes in RHI from baseline and each of the additional efficacy endpoints.

The principal investigator and a biostatistician will confirm the detailed statistical analysis plan before the database is locked. All *p* values will be two-sided. *P* < 0.05 will be considered statistically significant. No adjustments for multiple comparisons will be regarded. All statistical analyses will be performed in SAS v. 9.4 (SAS Institute, Cary, NC, USA).

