### Randomization

All participants who signed informed consent and met the enrollment criteria will be randomly assigned (1:1) either to the ipragliflozin treatment or the non-SGLT2is (control) group (Fig. 2). Treatments will be assigned via a web-based program, the minimization method, and biased coin assignment balancing by age (< 70 y; ≥ 70 y), HbA1c level (< 7%; ≥ 7%), current smoking (yes, no), pre-testing RHI (< 1.67; ≥ 1.67), and eGFR (< 45 mL/min/1.73 m^2^; ≥ 45 mL/min/1.73 m^2^) at the time of screening.

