This trial had several limitations that were also inherent to similar earlier investigations performed by our study team [37, 69]. First, we did not use a double-blind placebo-controlled trial here but rather an open-label design. This configuration might create an unexpected bias towards assessing potentially subjective endpoints associated with the treatments selected by the investigators. This bias could occur despite the strict requirement that the background medications of all participants must not change throughout the study. Second, the trial sample size is relatively small and the study treatment period is comparatively short. Third, the ANCOVA is set as the primary analysis based on our preliminary presumption of a negative correlation between the LnRHI values and their changes from baseline. We did not establish the correlation coefficient required to calculate the sample size. Hence, we estimated the sample size via a conservative two-sample *t*-test. Fourth, although the RH-PAT examination is non-invasive, easy to perform, and operator-independent, its output is sensitive to individual physical conditions and the ambient environment. To minimize these influences across all participating institutions, investigators must perform the RH-PAT examination in accordance with the operating manual provided by the manufacturer. Further, the present study excludes patients with RHI ≥ 2.10 according to the RH-PAT test performed prior to randomization. This threshold was previously proposed for normal endothelial function. Its border zone was ≥ 1.6 and < 2.10 [32]. The widely accepted cutoff value of RHI is 1.67 for the discrimination of normal and abnormal endothelial function [36]. Thus, changes in RHI in response to the treatments in the present study may differ depending on the baseline level. Therefore, we will attempt to assess the relative impacts of these effects using subgroup analyses as the primary endpoints and responder/non-responder analyses as the secondary endpoints. Finally, as SGLT2is are pharmacologically active in the kidney, their glucose-lowering effect may be insufficient in patients with lower eGFR [70]. However, the renoprotective efficacy of SGLT2is may be independent of glycemic control [25]. At this time, ipragliflozin is not recommended in diabetic patients with severe renal dysfunction such as eGFR < 30 mL/min/1.73 m^2^. Therefore, the inclusion criteria of the present trial align with the official indications for ipragliflozin.

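### Secondary endpoint (i), the % change in LnRHI, is given an unadjusted two-sample t test while every other efficacy endpoint is baseline-adjusted; ANCOVA would be more efficient if the presumed baseline correlation holds

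*Protocol article*

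**What the plan says.** All of the following is in the protocol article.

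- **Secondary endpoint (i)** (Statistical analysis plan): "i) the % change in LnRHI from baseline to 24 wks or discontinuation will be analyzed by a two-sample" t test. The text continues: "Their LSMs and 95% CIs will be calculated and the treatment effects will be compared between groups".
- **Primary endpoint** (same section): "The baseline-adjusted least-square means (LSM) and their 95% confidence intervals (CI) will be estimated by analysis of covariance (ANCOVA) for the FAS".
- **Additional efficacy endpoints** (same section): "Changes in the additional efficacy endpoints from baseline to 24 weeks or discontinuation will be analyzed by ANCOVA as for the primary endpoint".
- **Responder endpoints** (same section): a "logistic regression model adjusted by the corresponding baseline values to calculate the odds ratios and their 95% CIs".
- **Reason for ANCOVA** (Discussion, limitations): "the ANCOVA is set as the primary analysis based on our preliminary presumption of a negative correlation between the LnRHI values and their changes". The article adds that the correlation coefficient was not established, and that the sample size was therefore based on a two-sample t test, which it calls conservative.
- **Allocation** (Randomization): "the minimization method, and biased coin assignment balancing by age", HbA1c, current smoking, pre-testing RHI (cut at 1.67) and eGFR.

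**The concern.** Endpoint (i) is built from the same two RH-PAT readings as the primary endpoint, yet it is the only efficacy comparison described without adjustment, and no reason is given. If baseline predicts the outcome, an unadjusted comparison leaves that variation in the residual. The interval is then wider than it need be, and endpoint (i) could miss an effect that the primary analysis detects merely because the method differs. When allocation is balanced on factors that predict outcome and the test ignores them, the test also tends to reject slightly less often than its nominal level.

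A second, smaller matter is the reference to LSMs. Elsewhere in the section LSMs come from ANCOVA. For endpoint (i) the reader cannot tell whether they come from an adjusted model or are simply the group means.

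**Working it through.** **Step 1: the plan's own figure.** Inputs from Sample size estimation: difference 0.10, SD 0.15, two-sided α 0.05, power 90%. The normal formula 2(1.960 + 1.282)² × (0.15/0.10)² gives 47.3, so 48 per arm (96 in all). The exact noncentral t calculation gives 48.26, so 49 per arm, or 98, as stated. Power at 49 per arm is 90.4%. The sample size is thus sound for an unadjusted comparison of absolute change. The article makes no separate power claim for % change.

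**Step 2: what adjustment is worth in principle.** If baseline has correlation r with the outcome within arms, ANCOVA's residual SD is SD × √(1 − r²), so the t test's interval is wider by the factor 1/√(1 − r²). The article gives no r, so a range is assumed. The powers use the plan's 0.10 and 0.15 with 49 per arm.

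| \|r\| | t-test CI width relative to ANCOVA | ANCOVA power |
|---|---|---|
| 0 | 1.00 | 90.4% |
| 0.2 | 1.02 | 91.5% |
| 0.3 | 1.05 | 92.8% |
| 0.5 | 1.15 | 96.5% |
| 0.7 | 1.40 | 99.6% |

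**Step 3: does dividing by baseline remove the dependence?** No. A constant gain of 0.10 in LnRHI is 0.10/ln(1.67) = 19.5% at RHI 1.67, but 0.10/ln(2.10) = 13.5% at RHI 2.10. A uniform benefit on the log scale is therefore a baseline-dependent benefit on the % scale.

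**Step 4: simulation on the % scale.** From the plan: difference 0.10, SD of change 0.15, RHI below 2.10, 98 analysed patients. The baseline distribution is assumed, because the article gives only the upper limit. Between-patient SD of LnRHI was 0.12 to 0.20 throughout.

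| Assumed lower limit of RHI | t-test power | ANCOVA power |
|---|---|---|
| 1.2 | 86-87% | 90-92% |
| 1.05 | 71-73% | 78-85% |

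ANCOVA standard errors were 7-18% smaller, and the gain was roughly 3 to 12 points.

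A separate run had no lower limit and adjusted for baseline LnRHI only (mean LnRHI 0.5-0.6 before truncation, 1500 trials per scenario). Its five scenarios gave:

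- t test to ANCOVA power: 67% to 79%, 74% to 80%, 87% to 93%, 26% to 35% and 43% to 46%;
- correlation of % change with baseline: −0.30 to −0.54;
- standard errors: 6% (15.727 to 14.794) to 17% (9.004 to 7.432) smaller.

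**Step 5: type I error.** With 96 analysed, a lower limit of 1.2 and allocation balanced on RHI category only, the t test rejected in 3.5-4.9% of null trials and ANCOVA in 4.3-5.5%. Simulation error is √(0.05 × 0.95/1500), about 0.6 points. The t test is at or slightly below its nominal level. Five-factor biased-coin minimization was not simulated.

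**The case against.** The case for leaving the text alone has real force, and it rules out several stronger readings.

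- **A reader might infer that the t test and the LSMs are contradictory analyses.** They need not be. In a linear model with treatment only, LSMs are the raw group means and the p value equals that of the pooled t test. The article writes of baseline-adjusted LSMs for the primary endpoint and only of LSMs here, which fits an unadjusted model. The wording is ambiguous, not contradictory.
- **A reader might infer that the article itself says adjustment is needed for endpoint (i).** It does not. It presumes a correlation, for absolute change, and chooses ANCOVA for the primary analysis.
- **A reader might infer that the t test is invalid.** It is not. Nothing here shows bias or inflated type I error; the issue is efficiency.
- **A reader might infer that % change must depend on baseline at least as strongly as absolute change.** In one of the five scenarios without a lower limit it did not (correlation −0.40 against −0.53).
- **The scale may matter more than the covariate.** With median RHI 1.7 and between-patient SD 0.20, lowering the assumed limit from 1.2 to 1.0 took t-test power from 86% to 50% and ANCOVA from 90% to 55%. With SD 0.12, the falls were 84% to 69% and 92% to 82%. Adjustment helps, but it does not cure division by a quantity close to zero: at RHI 1.1 the same 0.10 is a 105% change.
- **The detailed analysis plan is confirmed before database lock**, and the model behind an LSM is a detail that can sit there. That answers the LSM ambiguity but not the choice of test, which the article names outright.

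What remains is that endpoint (i) alone is unadjusted, without a reason, although the data for adjustment are collected.

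**Conclusion.** The point holds as an available gain in efficiency, not as an error that threatens validity. If the article's presumption of a negative correlation is right, the t test is the less efficient choice for endpoint (i) and can be slightly conservative. Under the assumed baseline distributions with a lower limit on RHI, ANCOVA's standard errors are about 7-18% smaller and its power roughly 3 to 12 points higher; the run without a lower limit agrees closely. These sizes rest on assumptions about baseline RHI and on a correlation that the article says it did not establish. Near zero correlation there is little to gain. Because the endpoint is secondary and the primary analysis keeps ANCOVA, the trial's main conclusion is unaffected.

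**What to change.** In the Statistical analysis plan section, or in the detailed plan before database lock, replace the t test for endpoint (i) with ANCOVA containing treatment, baseline LnRHI as a continuous covariate and the allocation factors. Take the LSMs, 95% CIs and p value from that one model. Keep the t test, if wanted, as a supplementary unadjusted result.

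Write the covariates out; a cross-reference to the primary analysis would not settle them. The Abstract lists the five factors with RHI in two categories, while the Statistical analysis plan section speaks only of baseline adjustment and puts the allocation factors in a secondary analysis of variance.

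The cost is one sentence. Baseline LnRHI and the allocation factors are already collected, and no further patients are needed. The instability of a percentage of LnRHI at low RHI needs its own decision.

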**Methods:**

The PROCEED trial is an investigator-initiated, prospective, multicenter, open-label, randomized-controlled trial. The target sample size is 110 subjects. After they furnish informed consent and their endothelial dysfunction is confirmed from their decreased reactive hyperemia indices (RHI), eligible participants with T2D (HbA1c, 6.0–9.0%) and established CKD (30 mL/min/1.73 m^2^ ≤ estimated glomerular filtration ratio [eGFR] < 60 and/or ≥ urine albumin-to-creatinine ratio 30 mg/g Cr) will be randomized (1:1) to receive either 50 mg ipragliflozin daily or continuation of background treatment (non-SGLT2i). The primary endpoint is the change in RHI from baseline after 24 weeks. To compare the treatment effects between groups, the baseline-adjusted means and their 95% confidence intervals will be estimated by analysis of covariance adjusted for HbA1c (< 7.0% or ≥ 7.0%), age (< 70 y or ≥ 70 y), RHI (< 1.67 or ≥ 1.67), eGFR (< 45 mL/min/1.73 m^2^ or ≥ 45 mL/min/1.73 m^2^), and smoking status. Prespecified responder analyses will be also conducted to determine the proportions of patients with clinically meaningful changes in RHI at 24 weeks.

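### The responder logistic models leave out four of the five minimisation factors; the test stays valid but can lose a few points of power if those factors predict the change in LnRHI

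*Protocol article*

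**What the plan says.** The Randomization section of the protocol article assigns patients by "the minimization method, and biased coin assignment balancing by age" and then by "HbA1c level (< 7%; ≥ 7%), current smoking (yes, no), pre-testing RHI (< 1.67; ≥ 1.67), and eGFR". That makes five two-level factors.

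For the responder endpoints, the Statistical analysis plan section names a "logistic regression model adjusted by the corresponding baseline values", which is to supply odds ratios with 95% confidence intervals. No other covariate is listed for these endpoints.

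For the primary endpoint, the allocation factors appear in two places. The abstract's Methods describe an "analysis of covariance adjusted for HbA1c (< 7.0% or ≥ 7.0%), age (< 70 y or ≥ 70 y), RHI", followed by eGFR and smoking. The Statistical analysis plan section calls the primary ANCOVA baseline-adjusted and adds, as a secondary analysis, "an analysis of variance including allocation factors and treatment group as factors will also be performed".

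**The concern.** Minimisation keeps the arms alike on the factors it uses, so the true sampling variation of the treatment comparison shrinks to the extent that those factors predict outcome. A model that omits them still counts their contribution as random noise. The standard error is then too large for the design, and the test rejects less often than it should, both under the null and under the alternative. In a logistic model, leaving out a prognostic covariate also pulls the treatment odds ratio towards 1.

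The baseline value covers RHI, but nothing in the responder model stands in for age, HbA1c, smoking or eGFR. The abstract gives prominence to the responder analyses, so some avoidable loss of power on them is worth a line in the detailed analysis plan.

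**Working it through.** **The plan's own figure.** The protocol gives a sample size for the primary endpoint only: difference 0.10, SD 0.15, two-sided 5%, power 90%. The normal formula gives 2 × (1.960 + 1.282)² × (0.15/0.10)² = 47.3, so 48 per arm. The exact two-sample t-test needs 49 per arm (power 90.4%), that is 98, which agrees with the protocol. No figure is given for the responder endpoints.

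**Expected responders for (ii).** The arm means of 0.05 and 0.15 are those quoted under Sample size estimation from the planning of the earlier dapagliflozin study. The SD is 0.15, and baseline RHI is assumed.

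- Baseline RHI 1.67: a 15% rise in LnRHI is 0.15 × ln 1.67 = 0.077. Control: P(Z > (0.077 − 0.05)/0.15) = 43%. Ipragliflozin: P(Z > (0.077 − 0.15)/0.15) = 69%. Total: 49 × 0.43 + 49 × 0.69 ≈ 55 of 98.
- Baseline RHI 2.0: the threshold is 0.104, the proportions are 36% and 62%, and the total is about 48 of 98.

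About half respond. Endpoint (iv) contains everyone who meets (ii), so it has at least as many. With six terms (treatment, baseline, four factors), the smaller outcome category gives 43/6 ≈ 7 to 48/6 = 8 patients per term.

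**Simulation of (ii).** Settings: 98 patients; minimisation on five binary factors; biased coin 0.8 (assumed, since the protocol gives no probability); LnRHI with true SD 0.18 and test SD 0.106, so that the SD of change is √2 × 0.106 = 0.15; control change 0.05; effect 0 or 0.10; Wald test of treatment. Where two figures are shown, they come from separate sets of 2,500 and 4,000 trials, or of 1,200 trials for the second power pair at 0.10.

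| Effect of each of the four factors | Power, baseline only | Power, four factors added | Type I error, baseline only vs added |
|---|---|---|---|
| None | 73% | 74% | – |
| Shifts the change by 0.05 | 70%; 70% | 74%; 73% | 3.9% vs 5.1%; 4.5% vs 5.7% |
| Shifts the change by 0.10 | 61%; 62% | 71%; 70% | 2.7% vs 4.6% |
| Shifts the level by 0.05 | 74.2% | 75.3% | 5.4% for baseline only |
| Shifts the level by 0.10 | 74.2% | 75.8% | 4.5% for baseline only |

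Monte Carlo standard errors with 2,500 trials are √(0.7 × 0.3/2500) ≈ 0.9 points for power and √(0.05 × 0.95/2500) ≈ 0.4 points for type I error.

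**Check on the log-odds scale.** A second model set the factor effects as log-odds, with a responder rate of about 40%, a treatment log odds ratio of 1.2 and 3,000 trials per case.

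| Log-odds per factor | Type I error, baseline only vs added | Power, baseline only vs added | Median log odds ratio, baseline only vs added |
|---|---|---|---|
| 0 | 5.0% vs 5.5% | 74.3% vs 74.8% | 1.25 vs 1.31 |
| 0.5 | 4.2% vs 5.1% | 71.5% vs 74.0% | 1.17 vs 1.30 |
| 1.0 | 3.5% vs 5.7% | 62.4% vs 69.0% | 1.04 vs 1.31 |
| 1.5 | 2.7% vs 5.5% | 50.7% vs 64.8% | 0.89 vs 1.31 |

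The direction is the same. The last row gives each of four factors an odds ratio of e^1.5 ≈ 4.5 and serves only as an outer bound.

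**The case against.** The strongest reply is that a prespecified logistic model with the baseline value is a legitimate analysis of secondary endpoints that carry no multiplicity control, and that adding covariates is a matter of preference. That largely stands: nothing here is invalid, and the baseline value probably covers the strongest predictor.

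The size of the loss can also be challenged. If age, HbA1c, smoking and eGFR act on the level of LnRHI at both visits, the baseline value already carries most of their effect and only 1 to 2 points are lost. The 8 to 10 point loss needs each factor to shift the change by as much as the assumed drug effect. With assumed group shares of 0.5, 0.5, 0.25 and 0.3, it would also raise the SD of change to √(0.15² + 0.10² × 0.8975) ≈ 0.18, against the plan's 0.15. This objection stands too.

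A reader might infer that the plan contradicts itself by using different covariates for primary and responder analyses. That holds only against the abstract. In the body, the primary ANCOVA is described as baseline-adjusted and the allocation factors enter a secondary analysis of variance, so on that text the responder models match the primary one.

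The full covariate list could also be left to the detailed analysis plan, which is to be confirmed before database lock. But the article does state a covariate for the responder models, so there is a stated choice to comment on.

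Finally, the remedy is not free. In the log-odds runs the larger model's type I error reached 5.7% by the Wald test and 6.6% by the likelihood ratio test.

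**Conclusion.** The point holds as a minor one about efficiency. The responder models omit four factors on which allocation is balanced. The consequence, if those factors predict the change in LnRHI, is a conservative test, less power and an odds ratio nearer 1. For endpoint (ii) the loss is about 3 to 4 points at a shift of 0.05 per factor, 8 to 10 at an unsupported 0.10, 1 to 2 if only the level is affected, and essentially nil if the factors are not prognostic.

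These figures rest on assumptions the protocol does not supply: the coin probability, the factor shares and effects, the baseline distribution, and arm means taken from another study's planning.

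Two stronger readings are not supported. Omitting the factors does not raise the false-positive rate; the bias is towards caution. Nor can one say that the responder tests run below the nominal 5% in general: with non-prognostic factors, or factors acting on the level alone, the baseline-only model stayed close to 5%.

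**What to change.** In the detailed analysis plan, before database lock:

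- For endpoints (ii) and (iv), fit the logistic model with treatment, baseline LnRHI and the age, HbA1c, smoking and eGFR groups used in the minimisation. Keep the baseline-only model as a sensitivity analysis.
- For (iii) and (v), use the same covariates, with Firth's penalised likelihood if responders are few. This keeps one covariate set across four endpoints derived from the same measurement.

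The factors are already collected for allocation, so the cost is a few lines of text. The statistical price is four more parameters, with about seven patients in the smaller outcome category per term for (ii), a type I error that may run slightly above 5%, and an odds ratio that is conditional on the added factors and must be described as such.
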